#### Blinding

##### Who is blinded

This study follows a double-blind outcome-assessor design with participant blinding procedures in place. Both participants and researchers will be blinded to the group assignments to prevent bias. Any technical or logistical queries regarding the use of light loggers and the LightUP app will be addressed by a designated technical support team blinded to the group assignments. This arrangement will reduce the risk of unintentional unblinding through routine interactions and ensure that study integrity is preserved.

##### How blinding is achieved and maintained

Blinding is maintained by using two apps with identical appearance, naming, iconography, onboarding flow and data entry screens. Both apps collect the same light, sleep and mood data and interact identically with the ActLumus logger and Garmin tracker; only the intervention app contains the active behaviour-change features (feedback, goals, prompts), which are implemented via server-side logic not visible to participants or assessors. App store/package identifiers and version numbers are masked in participant-facing materials; installation is performed via a study link that deploys the correct configuration automatically. Staff who perform outcome assessments have no role in app provisioning. To evaluate blinding integrity, participants and assessors will be asked at the endpoint to guess the assigned group and rate their confidence.

##### Unblinding procedures

Unblinding will only be conducted in exceptional cases where it is necessary for safety or technical reasons:

Medical emergencies: In the event of a medical emergency where knowledge of the group assignment is essential for participant safety, the principal investigator (PI) will be notified. If deemed necessary, the PI will authorize a designated unmasked study personnel to access the randomization code by referring to the secure manual randomization listTechnical issues: Should significant technical issues arise with the LightUP app or light loggers, unblinding may be required to resolve the problem. Only the technical team, authorized by the PI, will be granted access to the randomization code to address the issue. Participants will remain blinded throughout this process and no data will be compromised as a result of technical unblinding

### Informed consent

Written informed consent will be obtained from all participants prior to any study procedures. Trained research staff at the Active Ageing Centres will explain the purpose, procedures, risks and potential benefits of the study using a standardised participant information sheet. Consent will be obtained in English or local dialects, depending on participant preference, and adequate time will be provided for participants to ask questions. Only participants who provide written, signed informed consent will be enrolled in the study.

Consent will cover the collection and use of self-report data, wearable device–derived light and activity data, cognitive performance measures and dried blood spot samples. Participants will be asked for permission for their anonymised data to be used in future ancillary studies and for sharing under open-access conditions (CC-BY). No biological samples will be stored beyond the planned vitamin D analyses.

### Intervention

#### Experimental intervention

The experimental intervention is the LightUP mHealth smartphone application (app), which is downloaded onto participants’ own smartphones and used for 12 weeks, following a 4-week baseline monitoring phase. Participants in the intervention group will also wear a pendant-worn ActLumus light logger and a wrist-worn Garmin Vivosmart 5 activity tracker throughout the intervention period.

The LightUP app delivers evidence-based behaviour change techniques, including personalised feedback, self-monitoring, goal setting, and educational messages related to healthy light exposure. Participants are able to view their daily light exposure levels directly within the app, supporting self-monitoring and awareness of light-related behaviours. The app was co-designed with older adults and community service providers using a participatory, user-centred approach. The co-design process and development framework have been described in a previously published protocol paper [19].

Data from the ActLumus light logger are integrated into the app to tailor recommendations and to support participants in meeting daily and weekly light exposure targets. The app incorporates simple reward features, such as the awarding of trophies, to reinforce engagement and goal attainment. To support sustained engagement, participants receive a mid-intervention drop-in session during the intervention period.

#### Control intervention

The comparator is a placebo version of the LightUP app, which collects light, sleep, and mood data but does not provide behaviour change components such as personalised feedback, prompts, or goal-setting features. Instead, the placebo version retains the same data logging functions and presents neutral content and generic notifications to maintain engagement without directing behaviour.

Both the intervention and placebo versions share a similar interface, navigation structure, and notification timing, ensuring a comparable user experience across groups. Participants in the comparator group also wear the ActLumus light logger and Garmin Vivosmart 5 activity tracker, ensuring equivalent monitoring between groups and isolating the behavioural components of the intervention. Following the 12-week intervention period, participants in both groups enter a 12-week follow-up phase, which includes 2 weeks of extended monitoring.

##### Rationale for comparator

We selected a placebo version of the LightUP app as the comparator to ensure blinding and to isolate the specific effects of the behavioural intervention. Both groups use the same wearable devices (light logger and activity tracker) to monitor light, activity and sleep, but only the intervention group receives active features including personalised feedback, prompts and education. This design allows us to control potential confounding effects of self-monitoring and study participation while testing whether the behavioural features of the LightUP app confer additional benefit. As no standard of care currently exists for promoting light exposure in community-dwelling older adults, a placebo app was chosen over usual care to enhance methodological rigour.

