**Methods:**

The trial is a community-based, double-blind, parallel-group randomised controlled trial involving approximately 90 community-dwelling older adults (≥ 60 years) recruited through Active Ageing Centres in Singapore. Participants will be randomised using a secure web-based system with stratification by age, sex and recruitment site to receive either the active LightUP app with behaviour change features (goal setting, self-monitoring, personalised feedback) or a placebo version without these features. The primary outcome is daily time above 250 lx melanopic equivalent daylight illuminance (melanopic EDI) during daytime, measured with the ActLumus light logger across baseline, intervention and follow-up periods. Secondary outcomes include sleep parameters and circadian rest-activity rhythms, sleep quality, mood, cognition, frailty status, physical activity, body composition and vitamin D levels. The usability and acceptability of the LightUP app and wearable devices will also be assessed. Analyses will follow the intention-to-treat principle, supplemented by per-protocol analyses. Generalised linear mixed models will be used for repeated measures, with multiple imputation for missing data and exploratory Bayesian analyses. All analyses will be pre-registered on the Open Science Framework and de-identified datasets and code will be openly shared under a CC-BY license.

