### Participant timeline

The participant timeline and flow through the study are visualised in *Supplementary Fig. 1*. Following eligibility screening, obtaining informed consent, and documenting sociodemographic and health characteristics at Week 1, participants undergo a 4-week baseline monitoring period (weeks 1–4). During this period, they wear the ActLumus light logger and Garmin Vivosmart 5 activity tracker.

Following the baseline monitoring period, participants undergo baseline assessments (week 4) and are randomised in a 1:1 ratio to either the intervention or comparator arm.

The intervention phase lasts 12 weeks (weeks 4–16). Participants in the intervention group use the LightUP mHealth app, which delivers personalised feedback, education and goal setting, while participants in the comparator group use the placebo version of the app that records but does not provide feedback. Both groups continue to wear the ActLumus logger and Garmin device throughout this period. An additional drop-in session is delivered at week 10 to reinforce adherence.

A follow-up period of 12 weeks (weeks 17–28) follows the intervention. During this time, participants no longer use the app but continue their usual monitoring and assessments. The follow-up includes a 2-week monitoring phase with both the ActLumus and Garmin devices to assess sustained changes in light exposure, sleep and circadian rhythms.

Assessments are scheduled at four key time points:

Week 4 – Baseline assessment (BL): sleep quality (PSQI), mood (BMIS), cognition (NIH Toolbox), frailty (five criteria), physical activity (PASE), body composition, vitamin D (25(OH)D)Week 10 – Midpoint assessment (MP): interim assessments of sleep, mood, cognition, frailty, physical activity, body composition and vitamin DWeek 16 – Endpoint assessment (EP): repeat assessments including usability (MAUQ), acceptability (TAM, TFA) questionnaires and qualitative post-trial discussionWeek 28 – Follow-up assessment (FU): repeat full assessments, including 2 weeks of device-based monitoring

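### The comparator rationale claims control for self-monitoring, but as the arms are described self-monitoring of light is part of what differs between them, so benefit beyond self-monitoring cannot be claimed

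*Protocol article*

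**What the plan says.** The section Rationale for comparator (Protocol article) explains the choice of a placebo app. It notes that both groups wear the same devices and that only the intervention group receives the active features. It then states: "This design allows us to control potential confounding effects of self-monitoring and study participation". In the same sentence it gives the purpose as "testing whether the behavioural features of the LightUP app confer additional benefit". Control intervention makes a related claim, that equal monitoring in both groups isolates the behavioural part of the intervention.

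Other sections describe what each arm receives:

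- Abstract, Methods: participants are randomised to the "active LightUP app with behaviour change features (goal setting, self-monitoring, personalised feedback) or a placebo version without these features".
- Experimental intervention: "The LightUP app delivers evidence-based behaviour change techniques, including personalised feedback, self-monitoring, goal setting, and educational messages". The same section adds: "Participants are able to view their daily light exposure levels directly within the app, supporting self-monitoring and awareness of light-related behaviours".
- Control intervention: the placebo app "does not provide behaviour change components such as personalised feedback, prompts, or goal-setting features". It keeps the logging functions and shows neutral content and generic notifications.
- Participant timeline: controls use the "placebo version of the app that records but does not provide feedback".

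**The concern.** A design controls for a factor when both arms have it to the same degree. The comparator rationale treats self-monitoring as such a factor. The Abstract treats it as one of the ingredients that only the active arm receives, and Experimental intervention names the means of delivery: seeing one's own light levels in the app. One term cannot be both a balanced background factor and a component under test.

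What is at stake is the reading of a positive primary result. Reported under the comparator rationale, it would be taken to mean that goals, prompts, feedback and education work over and above self-monitoring. If controls do not see their light readings, the same result could come partly or wholly from showing people those readings. The distinction matters for anyone who wants to know which parts of the app to keep, and the Limitations section does not mention it.

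**Working it through.** No formula or planned figure is involved, so the check sets the descriptions of the two arms side by side.

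| Element | Active app | Placebo app | Where stated |
|---|---|---|---|
| Wearing the light logger and activity tracker | yes | yes | Control intervention; Rationale for comparator |
| Light, sleep and mood data collected by the app | yes | yes | How blinding is achieved and maintained; Control intervention |
| Notification timing | shared | shared (generic content) | Control intervention |
| Scheduled assessments | yes | yes | Participant timeline |
| Self-monitoring, named as a feature | yes | no | Abstract, Methods |
| Viewing own daily light levels | yes | not stated; recording without feedback | Experimental intervention; Participant timeline |
| Personalised feedback, goals, prompts | yes | no | Control intervention; How blinding is achieved and maintained |
| Education | yes | no | Rationale for comparator |
| Trophies as rewards | yes | described for the active app only | Experimental intervention |

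**Step 1: what is balanced.** Device wear, being observed, logging of sleep and mood, notification timing and the assessment schedule. The phrase about study participation in the comparator rationale is therefore sound.

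**Step 2: what is not balanced, as described.** Self-monitoring of light. The Abstract puts it on the active side only, and the one mechanism given for it (seeing one's light levels) is described only for the active app. The primary outcome is itself light exposure, so this is the form of self-monitoring that bears on the primary result.

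**Step 3: what the contrast can identify.** Let D be the true difference between arms in the primary outcome. Let s be the part due to seeing one's own light values, and r the part due to everything else in the active package, including any interaction with s.

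- If light values are withheld from controls, D = s + r. Two arms allocated 1:1 estimate D. There is no arm with light display alone, so s and r cannot be separated.
- If light values are shown to controls, s is present in both arms and D = r. The claim in the comparator rationale would then hold, but the Abstract would be wrong and Experimental intervention misleading.

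The stated inference is about r. The arms as described deliver D = s + r.

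**Step 4: what is untouched.** The sample size section concerns the detectable difference between arms (a 20% change, about 20 min/day for the primary metric). That is a statement about D, and nothing above alters it.

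**The case against.** The strongest defence is that self-monitoring is used loosely in the comparator rationale and means only wearing the loggers and recording one's own data. The sentence just before it is about shared devices, and both arms do log sleep and mood. On that reading the statement is true. What stands is that part of self-monitoring in the broad sense is indeed balanced. What does not stand is the reading itself: the Abstract and Experimental intervention use the term for an active ingredient and tie it to seeing one's light levels. If only being monitored was meant, the sentence still needs rewording.

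A second objection is that no sentence says controls cannot see their light values. This is correct. The withholding is inferred from the Abstract and from Participant timeline, and feedback need not mean display. The lists of withheld features in Control intervention, in the blinding section and in the comparator rationale itself do not name self-monitoring or light display, although those in Control intervention and the rationale are worded as examples. Outright exclusion of self-monitoring from the placebo rests on the Abstract alone. So a reader who infers as settled fact that controls are denied sight of their data goes further than the text does. The sections still disagree whichever way the fact turns out.

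A third objection is that the trial does not formally claim a component effect. Objectives and Primary outcome already speak of the effectiveness of the app as a whole, and the primary model tests group by assessment block. This stands, and it limits the point to the comparator rationale and the matching remark in Control intervention.

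**Conclusion.** The comparator rationale claims an inferential property that the arms, as described, do not have. The randomised contrast estimates the LightUP package, including self-monitoring of light, against a placebo logging app. It does not support a statement of benefit beyond self-monitoring.

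The consequence is one of attribution and has no numerical size. One might be tempted to say that anything from none to all of the targeted 20 min/day could be due to displaying light readings. That only restates that s and r are not separately identified; it is not an estimate, and the protocol gives nothing from which to make one. Nor should a reader infer that the comparison is confounded or the trial invalid: the randomised comparison is valid for the package, and effect size and sample size are unaffected.

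The conclusion about attribution assumes that light values are withheld from controls, as the Abstract and Participant timeline imply. If they are shown, the rationale is right and those other sections are not. That the sections contradict each other does not depend on this assumption.

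**What to change.** First confirm what light data, if any, the placebo app shows its users. Then reconcile the sections.

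- **If light values are withheld:** reword Rationale for comparator to say that the design controls for device wear, being observed, logging and notifications. Drop the claim of control for self-monitoring, and with it the implication of benefit additional to it. Adjust the remark in Control intervention about isolating the behavioural part. State the primary conclusion as the effect of the full LightUP package, including self-monitoring of light, against a placebo logging app.
- **If controls do see their light values:** leave the rationale and correct the Abstract, Experimental intervention and Participant timeline, so that viewing light levels is shown as common to both arms.

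The cost is wording only. Design, data collection and power do not change. In the first case the claim becomes somewhat less specific. The separate statistical analysis plan is to be finalised before data analysis, so the wording of the primary conclusion can also be fixed there.

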#### Criteria for discontinuing or modifying allocated interventions

Participants may withdraw from the allocated intervention at any time, either at their own request or if adverse events, discomfort, or technical difficulties occur. In such cases, participants are invited to continue follow-up assessments unless they withdraw consent entirely. The intervention protocol is standardised and no modifications to the app are anticipated beyond its automated, data-driven feedback features. All instances of discontinuation or protocol deviation will be recorded.

#### Strategies to improve adherence

Adherence is supported through multiple strategies. The LightUP app incorporates reminders, progress-tracking features and personalised prompts to encourage consistent use. Research staff provide technical support for device setup, troubleshooting and ongoing use, including in-person onboarding with the wearable devices and LightUP installation, in-app tutorial, and a printed step-by-step participant booklet. Ongoing assistance is available via WhatsApp or phone, with in-person support provided on a needs basis. In addition, cloud-based data streams are monitored to identify issues such as failed syncing, battery depletion or limited app interaction, enabling timely follow-up. A mid-intervention drop-in session is conducted to maintain engagement. Overall, adherence and quality control of device and app-related components is monitored through app usage logs, wearable device data and completion of scheduled assessments.

#### Concomitant care

Participants are permitted to continue all aspects of their usual medical care, daily routines and lifestyle activities throughout the trial. However, concurrent participation in other mHealth intervention studies or trials targeting circadian rest-activity rhythms, sleep, mood, cognition, frailty, physical function, or vitamin D is not permitted, to avoid contamination and ensure that behavioural changes can be attributed to the LightUP app. All relevant changes in health status or treatments during the study will be documented.

### Outcomes

#### Primary outcome

The primary outcome is the effectiveness of the LightUP app in improving light exposure behaviour in older adults. This will be assessed using data from the ActLumus wearable light logger (ActLumus, Condor Instruments; São Paolo, Brazil) across the 4-week baseline, the 12-week intervention and the 2-week follow-up monitoring period. The primary analysis metric is the mean daily time (minutes per day) above 250 lx melanopic equivalent daylight illuminance (melanopic EDI) during daytime hours. Changes will be calculated relative to baseline and both short-term effects (during the 12-week intervention) and longer-term effects (during follow-up) will be examined.

#### Secondary outcomes

Secondary outcomes span multiple domains.

##### Sleep

Quantity and quality: total sleep time, sleep efficiency, sleep onset latency and wake after sleep onset, measured via Garmin Vivosmart 5 (Garmin Ltd., Olathe, KS, USA) actigraphy and sleep diaries throughout the study.

Subjective quality: assessed using the Pittsburgh Sleep Quality Index (PSQI) [26] at weeks 4 (baseline), 10 (midpoint), 16 (endpoint) and 28 (follow-up).

##### Circadian rhythms

Interdaily stability, intradaily variability and relative amplitude of rest-activity cycles, measured continuously with Garmin data across the study period.

##### Mood

Mood will be assessed using the Brief Mood Introspection Scale (BMIS) [27] at baseline, midpoint, endpoint and follow-up. Daily mood will be captured using the Single-Item Mood Scale (SIMS) [28]. Weekly mood ratings will be assessed using the Visual Analogue Mood Scale (VAMS) during the intervention.

##### Cognition

Cognitive performance will be assessed using the NIH Toolbox^®^ battery [29] at baseline, midpoint, endpoint and follow-up, including the Dimensional Change Card Sort, Flanker Inhibitory Control and Attention, Oral Symbol Digit, Picture Sequence Memory, Rey Auditory Verbal Learning and Pattern Comparison Processing Speed tests.

##### Frailty and physical activity

Frailty will be assessed using standard criteria (weight loss, exhaustion, low activity via Physical Activity Scale for the Elderly (PASE), slowness via 5-metre walk and grip strength [30]). Physical activity outcomes including daily step count, sedentary behaviour, moderate-to-vigorous activity will be assessed using Garmin wearable data.

##### Body composition

Body composition outcomes, including weight, body fat percentage, muscle mass, bone mass and body mass index (BMI), will be assessed at baseline, midpoint, endpoint and follow-up using a bioelectrical impedance analysis (BIA) machine (TANITA DC-430MA, Tanita Corporation, Tokyo, Japan).

